## Background

Cognitive disorders, such as Alzheimer disease, gradually leading to the dementia syndrome are the most important chronic illness group leading to increased need for assistance, disability and institutional care among older people
[1]. Dementia also augments stress and burden, and reduces quality of life (QoL) among caregivers
[2]. Usually, dementia patients wish to live at home as far as possible and the spousal caregivers are in the key role in enabling it. Therefore, there is an urgent need for developing supportive methods for coping, as well as effective psychosocial rehabilitation for patients with dementia and their caregivers alike.

Today, there is growing evidence that the most effective interventions for dementia are psychosocial interventions focusing on the needs of both patient and caregiver. Using these interventions, dementia families are provided with means to adapt and cope with dementia
[3]. Psychosocial interventions coach caregivers to help patients to use their remaining capacities to participate. Effective psychosocial interventions are built on co-operation between professionals and dementia families
[4]. By supporting mastery, self-efficacy and problem-solving skills of caregivers, these interventions aim to empower dementia families to cope with their everyday life, promote dignity and autonomy
[5]. Also, the concept of reciprocity in giving and receiving support has been highlighted
[6]. Many psychosocial studies demonstrate that individuals can be supported to maintain their skills and build resilience
[4,7,8].

Many health-promoting programs have used self-management methods and they have been shown to be effective in improving prognosis of chronic diseases including asthma,diabetes, and heart failure
[9,10]. Self-management can be defined as a person’s ability to organize his/her life under the influence of a chronic disease, to engage in activities and protect and promote health through knowledge. Self-management programs (SMP) combine biological, psychological and social intervention techniques to maximize functioning
[9,11]. In SMP, professionals support patients with a patient-centered approach to manage their care
[12,13]. This includes support of patient’s autonomy, decision making, problem-solving skills and responsibility
[5,12,14]. It places patient’s values, needs and priorities in the center of health care

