### Statistical analyses

Sample size was calculated based on the 15D measure
[22]. With an estimated standard deviation of 0.10, and type I error of 5%, and 80% power, 62 patients would be needed in each group to show a 10-point difference between groups. We estimated that 20% will drop out so we decided on 160 patients as a sample size. Data will be analyzed on an intention-to-treat basis. In baseline findings, the continuous variables and descriptive values will be expressed by means with standard deviations (SD) and medians with range. For the variables with a normal (Gaussian) distribution, statistical comparisons between the groups will be made by using an analysis of variance. If the variables have a non-normal distribution or ordinal level, statistical comparison between groups will be made using the Mann–Whitney U test. Measures with a discrete distribution will be expressed as percentages (%) and analyzed by chi-square or Fischer's exact test when appropriate. Imputation method of ‘the last observation carried forward’ (LOCF) and ‘worst-rank score’ principle will be used.

Since the distributions of health care costs are highly skewed, the differences between means and confidence intervals are estimated using the bootstrap method (bias corrected and accelerated bootstrapping).

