There are also challenges in this study. The population is old and frail with comorbidities and, therefore, prone to competing causes of complications and death. The intervention is delivered in a multifactorial and flexible format, so it is difficult to determine which aspects of intervention are efficacious. It is possible that there is heterogeneity in the continuation of meetings with group members after the eight weeks of organized meetings, which, with dropping out, may contribute to insufficient difference between the intervention and normal care groups. Contamination of the control group presumably is not a problem, because psychosocial group rehabilitation is rarely available for dementia patients and their caregivers in Finland. It is also challenging to know if the selected scales are suitable and sensitive to measure changes in self-efficacy, mastery, competence and especially HRQoL and depression in this heterogeneous group consisting of various stages of dementia.

The group dynamics and atmosphere are unique in each group. It may be possible that the dementia patient is happy in their group, but the caregiver feels burden or bored in their own group and, therefore, wishes to drop out of the intervention. It is important that the group leaders communicate with each other to know how the ‘other spouse’ works in the other group.

The trial follows common ethical principles in randomized trials. Participants are not exposed to risks, they receive verbal and written information before any study procedures, they participate voluntarily, and they may withdraw at any phase of the study. Individuals with dementia write an informed consent when they are capable of doing so; otherwise the spousal caregiver writes it on behalf of both of them. Control group members receive normal care offered by community. For the rehabilitation and study nurse visits, a risk/liability insurance is taken for participating dyads.

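### LOCF and worst-rank scoring are both prescribed with no rule for which missing values each one fills, and LOCF is a poor choice for the patients' 15D in a progressive condition

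*Protocol article*

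**What the plan says.** The Statistical analyses section of the protocol article settles missing data in one sentence: "Imputation method of ‘the last observation carried forward’ (LOCF) and ‘worst-rank score’ principle will be used". No outcome, visit or reason for missingness is assigned to either rule.

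The same section sets the context:
- Population: "Data will be analyzed on an intention-to-treat basis".
- Expected loss: "We estimated that 20% will drop out so we decided on 160 patients as a sample size".
- Tests: for normally distributed variables, "statistical comparisons between the groups will be made by using an analysis of variance"; otherwise, "If the variables have a non-normal distribution or ordinal level, statistical comparison between groups will be made using the Mann–Whitney U test".

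Under Outcome measurements, the primary outcomes are changes in the patients' 15D and in the caregivers' RAND-36 and SCQ. Study procedures and Table 1 schedule assessments at baseline, 3 and 9 months. The Background describes cognitive disorders as "gradually leading to the dementia syndrome". The Discussion expects deaths in an old, frail population and foresees that a patient may be content while "the caregiver feels burden or bored in their own group and, therefore, wishes to drop out of the intervention".

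**The concern.** The two rules make opposite assumptions about a person who is lost. LOCF credits a patient with no further decline. Worst-rank scoring places the same patient below everyone who was observed. Because neither rule is assigned, a missing 15D value could be handled either way, and the choice could be made after the results are known.

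LOCF is also weak on its own terms. It holds a patient with a progressive condition at an earlier score and enters the filled-in value as if it had been measured. If more 15D values are missing in one arm, that arm looks better for no reason related to treatment. The 15D is a primary outcome and the basis of the sample size, so both the estimate and the power are exposed.

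**Working it through.** **1. The plan's own figure.** Inputs from Statistical analyses: "With an estimated standard deviation of 0.10, and type I error of 5%, and 80% power", 62 per group, 20% dropout, 160 in total. Two-sided testing is assumed. The article's 10-point difference is not on the scale of an SD of 0.10. The stated 62 is reproduced with a difference of 0.05:

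n per group = 2 × (1.96 + 0.84)² × (0.10/0.05)² ≈ 62.7, or 63 by the exact calculation, against 62 stated.

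Inflating for dropout gives 62/0.8 = 78 or 63/0.8 = 79 per arm, so 156 to 158, against 160. I therefore use 0.05 as the reference difference. At 20% dropout, 0.8 × 80 = 64 of 80 values per arm would be observed and 16 filled in.

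**2. What LOCF estimates.** Let D be the mean decline without treatment, e the true effect, and p₁ and p₀ the proportions of intervention and control patients with a baseline value only (their LOCF change is 0). Then

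estimated difference = (1 − p₁)(−D + e) − (1 − p₀)(−D) = (p₁ − p₀)D + (1 − p₁)e.

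- No effect, D = 0.04, 25% v 15%: 0.10 × 0.04 = +0.004, which is 0.004/0.05 = 8% of the reference difference.
- No effect, D = 0.04, 30% v 10%: 0.20 × 0.04 = +0.008, or 16%.
- Range for D from 0.02 to 0.06 over both splits: 0.10 × 0.02 = +0.002 to 0.20 × 0.06 = +0.012.
- Equal 20% dropout, e = 0.05: 0 + 0.8 × 0.05 = 0.040.
- If patients miss only the 9-month visit and decline is linear (a further assumption), the value carried forward is from month 3 and two thirds of the decline is lost: 0.10 × 0.04 × 2/3 ≈ 0.003.

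D and the dropout splits are assumptions. The article gives only 20% overall.

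**3. Rejection with no treatment effect** (simulated, 80 per arm, SD 0.10, assumed baseline correlation 0.7, D = 0.04, dropout at random):

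| Dropout | t-test after LOCF | Mann–Whitney, worst rank for every dropout |
|---|---|---|
| 25% v 15% | 6–7% | 19% |
| 30% v 10% | 10–11% | 59–61% |

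A t-test on observed values alone rejected 5–6% throughout. The 19% lets the number of dropouts vary by chance; with the counts fixed at 20 and 12 it is 10–12%. With equal dropout, LOCF kept rejection at about 4–6%, so filling in values did not by itself raise the type I error here.

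**4. Power with a true effect of 0.05** (simulated, 80 per arm, change-score SD 0.10, D = 0.02 or 0.05, fixed dropout counts, baseline-only dropouts):

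| Dropout, intervention v control | ANOVA after LOCF | Mann–Whitney, worst rank for every dropout |
|---|---|---|
| 20% v 20% | 80% | 50% |
| 25% v 15% | 79–84% | 4% |
| 15% v 25% | 75–83% | 94% |

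Complete data give 88%.

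**5. Worst values in an ANOVA.** A rank is not a value on the 15D scale. If a worst score of 0 is substituted instead (baseline mean 0.80 assumed), the SD of change rises from 0.10 to about 0.32. Power at 20% equal dropout and a true effect of 0.05 is then about 0%.

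**The case against.** Several stronger readings are tempting, and the article does not support them.

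- **That both rules fill the same values.** The sentence says only that both will be used. Worst rank for deaths and LOCF for other gaps is a natural division in a population where deaths are expected. The article does not state that division either, and it would leave LOCF in place for withdrawals.
- **That the rules necessarily bias the comparison in opposite directions.** This needs unequal loss of outcomes. With equal loss, LOCF and a substituted worst score both shrink a true 0.05 to about 0.040.
- **That unequal loss is planned for.** The Discussion sentence concerns leaving the group sessions, and it is hedged. Under intention-to-treat, a couple who stop attending can still be assessed by the study nurses, and controls may withdraw too. The sentence makes unequal loss plausible, no more.
- **That the plan cannot analyse worst ranks.** It can. A variable with worst ranks is ordinal and non-normal, so the plan's own rule can send it to Mann–Whitney. The incompatibility arises only where ANOVA is kept.
- **That all three primary outcomes are affected alike.** RAND-36 and SCQ are measured on caregivers, who do not have the disease, and the Background remark describes the course of cognitive disorders, not the 15D over nine months.

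It can also be said that a condensed article leaves the allocation of rules to a fuller document. That is fair for the allocation alone. It does not cover LOCF, because the article itself chooses that method.

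**Conclusion.** The concern holds in limited form. The article prescribes two imputation rules without assigning them, and the choice between them can change the result: in the illustration with a true effect of 0.05 and 25% v 15% dropout, power is 79–84% under one and 4% under the other. That contrast takes the extreme reading in which every dropout receives the worst rank.

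LOCF alone does modest harm under the milder assumptions (a bias of 0.004 and 6–7% rejection at 25% v 15%) and more under the harsher ones (0.008 and 10–11% at 30% v 10%). With equal 20% dropout it removes a fifth of a true effect. These sizes depend on a decline, a correlation and dropout splits that are not in the article, and on dropouts having a baseline value only. They apply to the 15D; for RAND-36 and SCQ the unassigned rules matter, but the direction of any LOCF bias is not established. This should be fixed before the data are analysed. It is not a fatal flaw.

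**What to change.** Replace the imputation sentence with a rule for each analysis:

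- **Primary:** a likelihood-based repeated-measures mixed model for each primary score, using all observed 3- and 9-month values, with baseline as covariate and arm, visit and their interaction. No LOCF.
- **Sensitivity, deaths:** worst ranks for deaths only, analysed by a rank test and never by ANOVA.
- **Sensitivity, other missing outcomes:** a delta-adjusted analysis that makes missing values progressively worse, separately by arm, to show how far the data must depart from missing at random before the conclusion changes.

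State also that couples who leave the sessions are still assessed at 3 and 9 months, if that is the intention, and report missing outcomes by arm and reason.

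The cost is a change of wording and a little more programming; the visits are already scheduled. The drawback is that the primary analysis relies on missing at random, which would be doubtful if people leave because of how they are faring. Couples with no follow-up value also add nothing to the model's treatment estimate. The delta-adjusted analysis is there to address both.

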## Discussion

To our knowledge, this trial is the first one to test a support program of self-management among dementia families. We investigate in our trial the effects of an eight-week psychosocial group intervention to support the self-management skills of home-dwelling patients with dementia and their spousal caregivers. SMP intervention is compared with usual care. This intervention is provided for four hours per week in a day center. The group intervention is based on peer support, use of group dynamics and empowerment of participants to take active agency in their life. The SMP will encourage participants to identify their strengths and to enhance their problem-solving skills. This study also provides data on cost-effectiveness of the intervention.

There are several strengths in our study. First, all participants have an established diagnosis of dementia because they are recruited from memory clinics or after diagnostic procedures supervised by neurologists or geriatricians with CT or MRI scans, cognitive and laboratory tests. This is the diagnostic procedure recommended by national guidelines 2010
[20] and the Social Insurance Institution of Finland which controls the drug imbursements including all Alzheimer drugs. The national diagnostic scheme
[20] applied to practically all new Alzheimer cases ensures that diagnosis is in line with the Diagnostic and Statistical Manual of Mental Disorders, Fourth Edition (DSM-IV) and the National Institute of Neurology and Communicative Disorders and Stroke-Alzheimer’s Disease and Related Disorders Association (NINCDS-ADRDA) Alzheimer’s criteria. Second, all group leaders are trained very carefully and intensively. We tutor their work to ensure the uniform quality of the intervention, and also support the commitment of participants to the groups.

There are also challenges in this study. The population is old and frail with comorbidities and, therefore, prone to competing causes of complications and death. The intervention is delivered in a multifactorial and flexible format, so it is difficult to determine which aspects of intervention are efficacious. It is possible that there is heterogeneity in the continuation of meetings with group members after the eight weeks of organized meetings, which, with dropping out, may contribute to insufficient difference between the intervention and normal care groups. Contamination of the control group presumably is not a problem, because psychosocial group rehabilitation is rarely available for dementia patients and their caregivers in Finland. It is also challenging to know if the selected scales are suitable and sensitive to measure changes in self-efficacy, mastery, competence and especially HRQoL and depression in this heterogeneous group consisting of various stages of dementia.

The group dynamics and atmosphere are unique in each group. It may be possible that the dementia patient is happy in their group, but the caregiver feels burden or bored in their own group and, therefore, wishes to drop out of the intervention. It is important that the group leaders communicate with each other to know how the ‘other spouse’ works in the other group.

The trial follows common ethical principles in randomized trials. Participants are not exposed to risks, they receive verbal and written information before any study procedures, they participate voluntarily, and they may withdraw at any phase of the study. Individuals with dementia write an informed consent when they are capable of doing so; otherwise the spousal caregiver writes it on behalf of both of them. Control group members receive normal care offered by community. For the rehabilitation and study nurse visits, a risk/liability insurance is taken for participating dyads.

## Trial status

Patient recruitment is open.

## Abbreviations

ADL: Activities of daily life; BMI: Body mass index; CDR: Clinical dementia rating scale; CES-D: The center for epidemiologic studies depression scale; GHQ-12: 12-item general health questionnaire; HRQoL: Health-related quality of life; IADL: Instrumental activities of daily living; MMSE: Mini mental state examination; MNA: Mini nutritional assessment; NINCDS-ADRDA: National institute of neurology and communicative disorders and stroke-alzheimer’s disease and related disorders association; RAND-36: Measure of health-related quality of life; SCQ: The sense of competence questionnaire; SMP: Self-management program; QoL: Quality of life.
